### Data Management and Monitoring

All data will be collected on paper, entered into an Excel data entry format, and stored as digital data. The reason for this is that the intervention in this study involved self-monitoring of weight by app and encouraging behavioral change, so no significant safety issues are foreseen [38,39].

The research team will create a participant management sheet and continuously monitor the participants’ health and weight loss status during the supporters’ calls to identify any problems. During the study period, supporters will hold web-based meetings with the research team 1-6 times a month to share the participants’ situation, which will facilitate the detection of unexpected adverse events.

### Ethical Considerations

This protocol (version 6) and all related materials for this study were reviewed and approved by the Ethics Committee for Research on Life Sciences and Medicine Involving Human Subjects of Yokohama City University, Japan (approval General 2024-020) and by the National Ethics Committee in Health and Life Sciences of Côte d'Ivoire (RefNo 218-23/ MSHPCMU/CNESVS-km). In the event of a protocol change, the ethics committee and UMIN Clinical Trials Registry will be notified.

After receiving a full explanation face-to-face, the participant will be asked to sign an informed consent form. At the same time, the participant will be informed that she can withdraw her consent (Multimedia Appendix 2). The collected digital data will be password-protected, and the paper-based data will be stored in a locked cabinet. Additionally, the data for this research will only be accessible to the research team members who have been instructed to maintain strict confidentiality. The results of this research will be published in a peer-reviewed international scientific journal.

The study was registered in the UMIN Clinical Trials Registry (ID 000055142) (Multimedia Appendix 3).

## Results

In accordance with this protocol, the recruitment of participants started on August 26, 2024; by September 8, 2024, a total of 231 people were recruited. After reconfirming eligibility, one participant was excluded, and from 230 people, 108 were allocated to the intervention group and 108 were allocated to the control group. The baseline survey began on November 15, 2024, and is currently ongoing as of the end of November 2024.

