**Intervention**																					
	Distribution of scales					✓		✓													
	App installation and orientation					✓		✓													
	Health education via message app (1 time/wk)							✓		✓		✓		✓		✓		✓			
	In face-to-face health education (at the time of survey)					✓						✓						✓			
	Health education by phone							✓		✓				✓		✓					

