**Data collection for intervention group and control group**																					
	Weight, body fat percentage, and abdominal circumference measurements	✓				✓						✓						✓		✓	
	Height measurement	✓																			
	Structured interview	✓				✓						✓						✓		✓	

^a^The intervention lasted from months 0 to 6.

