### Outcome

The primary end point of the study is to compare weight changes from baseline to the end of the intervention (6 months later) between the intervention and control groups.

Secondary end points include the differences in body fat percentage, abdominal circumference, stage of behavioral change in weight loss behaviors such as diet and exercise, percentage of individuals with correct weight perception, degree of body pain (with visual analog scale [VAS]), and self-rated health at the end of the intervention (6 months later) compared to baseline. Simultaneously, the intervention group will be evaluated in terms of the frequency of inputs to the self-monitoring apps, degree of participation in WhatsApp groups, average number of steps taken, and degree of weight loss during the intervention period.

To evaluate the interim process of the intervention, the intervention and control groups will be compared and analyzed in the same manner as described above, 3 months after the start of the intervention. In addition, the intervention group will be evaluated for weight change at 1, 2, 4, and 5 months and for changes in the behavioral change stage of weight loss behaviors such as diet and exercise.

As a follow-up evaluation after the intervention, both groups will be evaluated at 12 months (6 months after the end of the intervention) in the same way.

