### Assignment, Allocation Concealment, and Blinding

The random assignment will be performed using the permuted block method. Stratification will be conducted based on BMI (threshold: 32 kg/m^2^) and age (threshold: 45 years), which represent the median values reported in a previous study. The four resulting strata will be as follows: (1) BMI ≥32 and age ≥45 years, (2) BMI ≥32 and age <45 years, (3) BMI <32 and age ≥45 years, and (4) BMI <32 and age <45 years.

The list of potential participants recruited was sent to study member allocator 1 in Japan. Allocator 1 prepares a provisional ID list that does not contain attributes other than BMI and age to ensure concealment and sends it to allocator 2. Allocator 2 creates an allocation table with an allocation ratio of 1:1 and BMI and age as adjustment factors using software for randomized controlled trial–stratified substitution blocks and allocates the provisional IDs to each stratum in descending order of provisional ID numbers, from top to bottom.

This study will be conducted in an unblinded manner. This is because the intervention group will be given a scale and an app to be installed; therefore, blinding of the participants will not be possible. In addition, the content of the questions asked during each evaluation differs between the intervention and control groups, making blinding difficult for supporters and research team members.

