### Data Collection Methods

Data will be obtained from supporters visiting the market to conduct face-to-face structured interviews (Multimedia Appendix 1) and anthropometric measurements. Body measurements will be taken at the time of recruitment to measure height and weight, and BMI will be calculated immediately. Subsequent data collection will include weight measurements, body fat percentage, and abdominal circumference. Height will be measured using a hardware SHUREMAN Lock Convex measuring tape (Kenoh Co, Ltd, Japan, model LC-5525) with a locking function, and an InBody (InBody Japan Inc, model H20N) will be used as the body composition scale. Structured interviews will be conducted using a questionnaire asking about sociodemographics, weight perception, behavioral change stages related to weight loss, behaviors related to weight management, body pain level (using the VAS scale), and the use of smartphone apps for weight management.

In addition, the intervention group will be asked about the weight and behavioral change stages of exercise and diet during the monthly telephone intervention.

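### The baseline weight in the primary endpoint is measured after allocation by unblinded supporters, and the pre-allocation weight is neither the endpoint baseline nor a covariate in kg

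*Protocol article*

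**What the plan says.** All references are to the protocol article.

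- **Endpoint.** The Outcome section sets the primary aim: "compare weight changes from baseline to the end of the intervention (6 months later) between the intervention and control groups". The Table 2 footnote runs the intervention from month 0 to month 6, so the start of the change is month 0.
- **Order of events.** Table 2 ticks eligibility and consent at month -2 and allocation at month -1. The row "Weight, body fat percentage, and abdominal circumference measurements" is ticked at months -2, 0, 3, 6 and 12. The Results confirm that allocation came first: "108 were allocated to the intervention group and 108 were allocated to the control group. The baseline survey began on November 15, 2024".
- **Earlier weight.** Data Collection Methods: "Body measurements will be taken at the time of recruitment to measure height and weight, and BMI will be calculated immediately". That BMI decides eligibility (30 or more) and the stratum (cut at 32).
- **Who measures.** Supporters do the interviews and the body measurements, and they also deliver the intervention. On blinding, the article says that "the content of the questions asked during each evaluation differs between the intervention and control groups, making blinding difficult for supporters".
- **What else happens at month 0.** Table 2 ticks scale distribution and app orientation at months 0 and 1. The row beginning "In face-to-face health education (at the time of survey" is ticked at months 0, 3 and 6.
- **Model.** Statistical Methods takes weight change as the dependent variable, with group, stratification variables and sociodemographic attributes as covariates. No weight in kg is listed.

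**The concern.** A baseline is protected by randomisation only if it is fixed before the arm can influence it. Here the value subtracted from every month-6 weight is recorded after allocation, by someone who knows the arm, at the visit where the intervention starts. Clothing, time of day, the order of steps at the visit and transcription to paper could each differ by arm. So could a real change in weight, if women already know their arm. A change score has no protection against this, because an error in the starting weight becomes an error of the same size in the outcome.

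The Limitations section acknowledges the lack of blinding. It does not mention that the baseline itself follows allocation. The reason given against blinding is the content of the questionnaire, which does not prevent weighing before the interview begins.

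**Working it through.** **1. The plan's own figure.** Inputs from Sample Size Calculation: difference 1.5 kg, SD 3.7 kg, z-values 1.96 and 0.842, dropout 10%.

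n per arm = 2 × (1.96 + 0.842)² × 3.7² / 1.5² = 2 × 7.851 × 13.69 / 2.25 = 95.5, so 96. Then 96 / 0.9 = 106.7, so 107. The t-test version gives 97 per arm, and 97 / 0.9 = 107.8, so 108. The stated 108 is reproduced, and nothing below changes it.

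**2. Which weight is baseline.** No single sentence says. The baseline-survey label in the Results, the month-0 column of Table 2, the six-month interval in Outcome and the weighing schedule in Recruitment all point to month 0. One detail points the other way: the Intervention section has the control group's height and weight measured at baseline, while Table 2 ticks height only at month -2.

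**3. How an error travels.** Let R, W0 and W6 be the recruitment, month-0 and month-6 weights. The planned contrast is

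mean(W6 − W0) in intervention − mean(W6 − W0) in control.

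If the intervention arm's W0 is shifted by b kg relative to control after allocation, with W6 unaffected, the contrast moves by −b. Adding R as a covariate while keeping W6 − W0 as the dependent variable leaves b in place. Taking W6 as the dependent variable with R as covariate removes W0, and so b, from the estimate.

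**4. Size, by assumption.** The article gives no value for b. With 97 evaluable women per arm, SE = 3.7 × √(2/97) = 0.531 kg. Two-sided type I error = 1 − Φ(1.96 − b/SE) + Φ(−1.96 − b/SE).

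| b (kg, assumed) | b / 1.5 kg | Type I error |
|---|---|---|
| 0 | 0% | 5.0% |
| 0.10 | 7% | 5.4% |
| 0.25 | 17% | 7.6% |
| 0.50 | 33% | 15.6% |

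**5. Direction.** An intervention-arm W0 recorded too high exaggerates the benefit. A real early loss in that arm before month 0 hides part of it.

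**The case against.** The strongest reply is that the mechanism is not shown to operate. The article does not say when women learn their arm. If they learn it at the month-0 visit, no arm-specific behaviour can come before it. The order of steps within that visit is also unstated. Table 2 is a monthly grid, and weighing first may already be the practice. Weight is read from a body composition device, which limits the measurer's influence. The lack of blinding is disclosed. All of this stands, and it is why the concern is an exposure to bias and not a demonstrated bias. It does not change the fact that allocation precedes the baseline weight, and an analysis plan that is not shown could not change that order either.

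A reader might go further in four ways that the article does not support.

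- **That the recruitment weight is ignored.** It sets eligibility and the BMI stratum, and the stratum enters the regression.
- **That women lost between allocation and month 0 leave the intention-to-treat analysis, and that the recruitment weight would bring all 216 back.** The article states intention to treat and does not give the handling of missing weights, which may sit in the analysis plan. A woman with no month-6 weight gains nothing from an earlier covariate.
- **That the 68 to 81 days from the recruitment window ("the recruitment of participants started on August 26, 2024; by September 8, 2024, a total of 231 people were recruited") to the opening of the baseline survey is the period at risk.** That period runs from allocation to baseline. Its dates are not given, and Table 2 shows one column, about a month.
- **That a woman's own supporter must not weigh her.** This presumes a fixed pairing of women and supporters that is not documented.

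**Conclusion.** The point holds as a weakness of design and analysis that is cheap to repair. The order of allocation and baseline, and the choice of change as the outcome, are stated in the article. That month 0 is the baseline is a firm inference from four consistent places, against one minor inconsistency.

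The exposure is one for one in the primary estimate, but its size and direction are unknown. The 7% to 33% range rests wholly on an assumed shift of 0.1 to 0.5 kg. The type I error figures also assume 97 evaluable women per arm, an SD of 3.7 kg and no true effect. They show sensitivity and do not predict bias.

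**What to change.** 1. State in the protocol which weight is baseline for the primary endpoint.
2. Analyse month-6 weight by ANCOVA, with group, the pre-allocation recruitment weight in kg and the stratification factors. Make this the primary analysis, or at least a prespecified sensitivity analysis reported beside change from month 0. The dependent variable must be month-6 weight, since adding the covariate to the change-score model does not remove the problem.
3. Instruct supporters to take and record weight first at each remaining baseline visit and at months 3, 6 and 12, before any arm-specific question, scale hand-over, app orientation or education. Baseline visits were still under way at the end of November 2024.

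**Cost.** Some analysis wording, one instruction to existing staff, and the notice to the ethics committee and registry that the article already promises for protocol changes. The recruitment weight exists for every allocated woman, because BMI was needed for eligibility and stratification. The statistical price is that it is about two months older than the month-0 weight by Table 2, and so should correlate slightly less with month-6 weight. Reporting both analyses shows how much that matters.

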## Discussion

### Expected Findings

The expected outcomes will analyze body weight, body fat percentage, and abdominal circumference. It is anticipated that the intervention group will achieve greater reductions in these three indicators compared to the control group. Additionally, the difference between the intervention and control groups is expected to be greater at 6 months and remain stable at 12 months.

### Comparisons With Prior Work

There are fewer community-based weight loss programs in sub-Saharan Africa than those conducted within health care facilities. One such program is that of Herrmann et al [25]; however, it primarily involves interventions led by health care professionals with specialized knowledge and does not use smartphones or web-based media.

In our study, we deliberately chose to use nonmedical staff as direct interventionists to evaluate the feasibility of implementing a weight loss program by those staff in sub-Saharan African countries where human resources in health care are particularly scarce.

Additionally, weight loss programs that use smartphone apps often recruit participants via web-based media, thereby primarily attracting individuals who are already motivated to lose weight [20]. Our study differs from previous research in that it targets communities with cultural norms that view being plump as a virtue, includes individuals who may not be aware of the need to lose weight, and recruits participants through face-to-face interactions.

To our knowledge, this is the first study to implement a smartphone app–based weight loss program in sub-Saharan Africa that does not require direct intervention by health care professionals and targets specific communities.

### Study Significance and Feasibility

The findings of this study will provide information on the effectiveness and feasibility of a smartphone app–based weight loss program for communities in sub-Saharan Africa. Additionally, it will offer evidence on the extent to which interventions led by nonmedical individuals can be effective.

In Côte d'Ivoire and neighboring countries, the most common occupation among women is merchant [40-43]. If the feasibility of using smartphone apps within this community is demonstrated, it could pave the way for applying it to other health programs. Furthermore, if the effectiveness of this program is confirmed, it has the potential to serve as a low-cost, sustainable weight loss model at the policy level.

### Limitations

First, the intervention cannot be blinded to the participants because those in the intervention group will receive a weighing scale. It is also difficult to make the supporters blinded because the questionnaires are different between the two groups. Second, it is not possible to perfectly prevent the participants from exchanging information with each other. However, we will try to understand the status of communications between the two groups by including a related question in the questionnaire. Third, the target population of the study may not represent all female merchants in Côte d'Ivoire as we only included those who have smartphones. However, as the smartphone ownership rate among female merchants in the market in the previous study was 77% [8], we judged this to be feasible.

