### Intervention

The weight loss intervention implemented in this study will target communities, including those who have no desire to lose weight, and will be low-cost without direct intervention by health professionals. The basic framework will be based on the American Heart Association (AHA)/American College of Cardiology (ACC)/The Obesity Society (TOS) guidelines for the management of overweight and obesity in adults [13] and the Burkina Faso program [25], which is implemented in the sociocultural context of West Africa. However, since both of these programs include direct intervention by health professionals, which differs from the purpose of this study, the content of the intervention is adapted to the situation in Abidjan in this study (Table 1). The weight loss intervention will be conducted for 6 months. The intervention will be based on self-weighing [11], which has been shown to be beneficial for weight loss, and will include the use of a low-cost personalized support smartphone app [16]. In addition, direct contact with the intervention group will be conducted by Ivorian non–medical professional supporters who were selected based on their research experience within Côte d'Ivoire and have received training for this study.

The intervention consisted of the following three components: (1) promoting weight measurement and encouraging self-monitoring through a smartphone app; (2) health education using a messaging app; and (3) in-person or telephone health education based on the stage of behavior change [26]. Lose it! (FitNow, Inc.) is a weight management app that will be used for weight self-monitoring [27], which has been used in weight loss programs in previous studies [20,28] and is available for free. WhatsApp, which is widely used in Côte d'Ivoire [29], can send and receive images, videos, audio, and text [30], and can deliver a variety of health education messages at low cost [31,32]. In addition, a step-counting app, such as Google Fit (Google Inc) for Android users and Health Care (Apple Inc) for iPhone users, can be installed for weight change and step-count monitoring. These apps will be installed on the smartphones of the intervention group, and participants will receive an orientation on their use. Additionally, they will be able to contact their supporters via WhatsApp to inquire about the use of Lose It! and another app at any time.

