Health education should include recommendations for and emphasize the importance of a healthy diet, exercise, and weight measurement. Diet and exercise content should be in line with the “Diet and Exercise” described in the “Obesity” chapter of the Côte d'Ivoire National Disease-Specific Cookbook Guidelines [33]. In-person or telephonic health education will be conducted once a month and tailored to the stages of behavioral change [26] (precontemplation, contemplation, preparation, action, and maintenance) of the target population. Interventions corresponding to the change process [34-36] of each stage are provided. The intervention stimulates interest in weight loss during the precontemplation stage, motivates implementation during the contemplation stage, supports implementation during the preparation stage, supports continuation during the action stage, and supports maintenance during the maintenance stage to maintain confidence in behavior. The intervention and evaluation schedules are shown in Table 2.

To maintain consistency among supporters in the intervention, a manual was developed on how to send health education material via WhatsApp. A manual for telephone interviews was developed, and supporters will conduct telephone interviews according to the manual and provide a report on the content of the interviews. Supporters will be trained on the content of the intervention and the survey to ensure the quality of the intervention and the survey.

No interventions are administered in the control group. For the control group, height and weight are measured at baseline and at data collection at 3, 6, and 12 months, and BMI is calculated and reported on the spot by the supporter. This allows participants in the control group to know their weight and BMI regularly. In addition, after the 12-month survey is completed, scales will be installed in the target markets free of charge so that participants can continue to measure their weights. In addition, we will introduce the app to those who wish to use it.

**Table 1 table1:** Adaptations of the weight loss program following the American Heart Association (AHA)/American College of Cardiology (ACC)/The Obesity Society (TOS) guidelines for the management of overweight and obesity in adults.

Variable	AHA/ACC/TOS guidelines [13]	Intervention adapted to this study	Reason for adaptation

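### Supporters both deliver the intervention and take the weight measurements, and the reason given for not masking them covers the interview but not the weighing

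*Protocol article*

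**What the plan says.** All of this is in the protocol article.

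- **Delivery.** Under Intervention, "direct contact with the intervention group will be conducted by Ivorian non–medical professional supporters", and for the coaching calls "supporters will conduct telephone interviews according to the manual". Table 2 adds a row for "In face-to-face health education (at the time of survey"), ticked at months 0, 3 and 6.
- **Measurement.** Under Data Collection Methods: "Data will be obtained from supporters visiting the market to conduct face-to-face structured interviews (Multimedia Appendix 1) and anthropometric measurements". For the control group, "height and weight are measured at baseline and at data collection at 3, 6, and 12 months", and the supporter tells the woman her BMI at once. Table 2 lists weight, body fat and abdominal circumference for both groups at months 0, 3, 6 and 12.
- **Reason for not masking supporters.** Under Assignment, Allocation Concealment, and Blinding: "the content of the questions asked during each evaluation differs between the intervention and control groups, making blinding difficult for supporters". The Limitations section repeats it: "It is also difficult to make the supporters blinded", again because of the different questionnaires.
- **Primary end point.** Under Outcome, the between-group comparison of weight change from baseline to 6 months.

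No separate assessor is described. The Limitations section mentions unmasked supporters but not that they both coach and measure.

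**The concern.** The stated obstacle to masking is the content of the questions. Standing on a scale or having the waist taped needs no arm-specific question, so the reason does not reach the primary outcome or the other body measurements.

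What is left is a staff role that measures the result of its own work while knowing the allocation. A digital scale limits reading error. It does not stop small differences in clothing removed, time of day or repeat weighing, and tape placement leaves more room still. Any such difference that arises between baseline and month 6 in one arm only is added to the estimated treatment effect. A larger sample would not remove it. The planned effect is only 1.5 kg, so a modest bias is not negligible beside it.

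**Working it through.** **1. Who does what, by visit (Intervention, Table 2, Data Collection Methods)**

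| Visit | Supporters give face-to-face education (intervention arm) | Supporters measure both arms |
|---|---|---|
| Month 0 | yes | yes |
| Month 3 | yes | yes |
| Month 6 (primary) | yes | yes |
| Month 12 | no | yes |

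At months 3 and 6, coaching and measuring share a visit. At month 12 the intervention is over, so only knowledge of allocation and past coaching remain.

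**2. Does the stated reason cover the measurements?** The reason is that the questions differ by arm. Table 2 gives the same measurements to both arms and Data Collection Methods names one body composition scale model, with no difference by arm. The reason therefore applies to the interview only.

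**3. The plan's own figure.** Inputs from Sample Size Calculation: difference 1.5 kg, SD 3.7 kg, z-values 1.96 and 0.842, dropout 10%.

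- Normal approximation: n = 2 × [3.7 × (1.96 + 0.842) / 1.5]² = 95.5, so 96 per group; 96 / 0.9 = 106.7, so 107.
- t-test version: 96.5, so 97 per group; 97 / 0.9 = 107.8, so 108.

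The stated 108 per group reproduces. The point does not alter it.

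**4. Illustration of bias.** The bias b is assumed, because the documents give none. It means the average between-arm error in weight *change*, over a whole arm.

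- SE = 3.7 × √(2/97) = 0.53 kg.
- Two-sided rejection rate with no true effect = Φ(b/SE − 1.96) + Φ(−b/SE − 1.96).

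| Assumed b (kg) | b as share of 1.5 kg | False-positive rate |
|---|---|---|
| 0 | 0% | 5.0% |
| 0.1 | 7% | 5.4% |
| 0.3 | 20% | 8.7% |
| 0.5 | 33% | 15.6% |

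**5. When b is zero despite unmasked weighing.** Table 2 places allocation at month −1 and the baseline measurement at month 0, so baseline weighing is unmasked too. If an arm-specific error e is the same at both visits, the error in change is e − e = 0. Only a difference that develops between baseline and month 6 enters b.

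**The case against.** The trial declares itself unblinded throughout and lists unmasked supporters as a limitation, so nothing is misstated or contradictory. That is right: this is an avoidable risk with a reason that falls short, not an inconsistency.

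A reader might infer that each woman is weighed by her own coach. The article does not say so. It shows overlap of role, not of individuals, and the Recruitment section, which mentions interviewers as well as supporters, leaves the division of duties unclear.

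Visit order, clothing rules and form layout may be set in manuals or in the survey form (Multimedia Appendix 1), which are not shown. Weighing may already come first. Their absence from an article is therefore no finding. The point rests on the role overlap and the reason that the article does state.

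There are safeguards: supporters are trained for survey quality, and one scale model is used. These narrow the room for error but do not separate coach from measurer.

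Masking would also be incomplete. Women may reveal their arm, and Data Management and Monitoring has supporters discussing participants with the research team 1 to 6 times a month. Pain and stage of change are reported by women who know their arm, so masking the measurer would not cure bias there. All of this stands and limits how much the fix can achieve. It does not make the stated reason apply to weighing.

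**Conclusion.** The point holds in a limited form. The supporter role delivers the intervention and takes the body measurements, including the primary outcome, and the only reason given for not masking it does not apply to those measurements. Own-coach weighing is neither stated nor excluded.

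The size is unknown. The range of 5.4% to 15.6% for a bias of 0.1 to 0.5 kg illustrates sensitivity. A reader might take it as the trial's expected error rate, but the documents give no basis for that. It assumes 97 analysed per arm, SD 3.7 kg, no true effect, and a bias that is absent or different at baseline. At 0.1 kg the harm is small.

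This is a worthwhile, inexpensive improvement. It does not invalidate the design or change the sample size.

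**What to change.** At months 3, 6 and 12, in both arms:

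1. Take weight, body fat and abdominal circumference first, under one standard procedure, before the interview, the arm-specific questions and any education.
2. Assign existing supporters so that, where feasible, no woman is measured by the supporter who coaches her, and the measurer does not hold the allocation list.
3. Amend Assignment, Allocation Concealment, and Blinding, Data Collection Methods, and Limitations to say so, and name the coach-assessor overlap as a limitation. If the manuals already set this order, stating it is enough.

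The article reports the baseline survey as still under way at the end of November 2024, so on its dates all three visits lay ahead.

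**Cost.** A visit rota and a fixed visit order, with existing staff and no change to 108 per group. Scheduling becomes slightly less flexible. Masking will be partial, and self-reported outcomes stay open to bias.
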